## Abstract

**Background:**

Extended criteria donors (ECD) are widely utilized due to organ shortage, but they may increase the risk of graft dysfunction and poorer outcomes. Hypothermic oxygenated perfusion (HOPE) is a recent organ preservation strategy for marginal kidney and liver grafts, allowing a redirect from anaerobic metabolism to aerobic metabolism under hypothermic conditions and protecting grafts from oxidative species–related damage. These mechanisms may improve graft function and survival.

**Objective:**

With this study, we will evaluate the benefit of end-ischemic HOPE on ECD grafts for livers and kidneys as compared to static cold storage (SCS). The aim of the study is to demonstrate the ability of HOPE to improve graft function and postoperative outcomes of ECD kidney and liver recipients.

**Methods:**

This is an open-label, single-center randomized clinical trial with the aim of comparing HOPE with SCS in ECD kidney and liver transplantation. In the study protocol, which has been approved by the ethics committee, 220 patients (110 liver recipients and 110 kidney recipients) will be enrolled. Livers and kidneys assigned to the HOPE group undergo machine perfusion with cold Belzer solution (4-10°C) and continuous oxygenation (partial pressure of oxygen of 500-600 mm Hg). In the control group, livers and kidneys undergoing SCS are steeped in Celsior solution and stored on ice. Using the same perfusion machine for both liver and kidney grafts, organs are perfused from the start of the back-table procedure until implantation, without increasing the cold ischemia time. For each group, we will evaluate clinical outcomes, graft function tests, histologic findings, perfusate, and the number of allocated organs. Publication of the results is expected to begin in 2021.

**Results:**

Dynamic preservation methods for organs from high-risk donors should improve graft dysfunction after transplantation. To date, we have recruited 108 participants. The study is ongoing, and recruitment of participants will continue until January 2020.

**Conclusions:**

The proposed preservation method should improve ECD graft function and consequently the postoperative patient outcomes.

**Trial Registration:**

ClinicalTrials.gov NCT03837197; https://clinicaltrials.gov/ct2/show/NCT03837197 ; Archived by WebCite® at http://www.webcitation.org/76fSutT3R

**International Registered Report Identifier (IRRID):**

DERR1-10.2196/13922

## Introduction

Transplantation is the ideal therapeutic treatment for end-stage liver and kidney disease. However, this treatment seems to be the victim of its own success. Although the number of liver transplantation (LT) and kidney transplantation (KT) procedures is increasing, as recently reported by the Italian registry, we face a dramatic decrease in the number of available organs [1].

Compared with standard donors, extended criteria donor (ECD) grafts are more vulnerable to the intracellular harmful effects of ischemia, such as a decrease in the availability of adenosine triphosphate (ATP), increase in reactive oxygen species, and release of lysosome enzymes with consequent alteration of cell structure and function [2,3]. In addition, hypoxia inhibits glucose oxidative phosphorylation, leaving anaerobic glycolysis as the only source of ATP production, with consequent alteration of the intracellular ionic environment and phospholipid membrane integrity [2,3]. All these events lead to the severe morphological damage that facilitates the onset of graft dysfunction [2,3].

Organ preservation is crucial when ECD transplant grafts are utilized. To date, static cold storage (SCS) is the most widely used method for organ preservation due to its simplicity and effectiveness in reducing metabolism and the associated oxygen need [4]. However, several studies have reported associations between the SCS preservation of ECD grafts and increased rates of delayed graft function (DGF) and primary graft non-function (PNF) in KT, increased rate of early allograft dysfunction (EAD) in LT, and reduced long-term graft survival [5,6].

Over the last decade, researchers have focused their attention on investigating alternative strategies for organ preservation. Preclinical and clinical studies have explored normothermic (35-37°C), sub-normothermic (20-25°C), and hypothermic (4-10°C) machine perfusion with (hypothermic oxygenated perfusion [HOPE]) or without (hypothermic machine perfusion) oxygen [3,7]. Dynamic perfusion improves the quality of high-risk grafts, removes waste products, and provides metabolic substrates for ATP and glutathione generation, which protects against reactive oxygen species–related damage [7]. Several clinical studies have demonstrated how HOPE improves short-term and long-term outcomes of KT and LT recipients [7-11].

In this study, we will evaluate the benefit of end-ischemic HOPE on ECD grafts (liver and kidney) as compared with SCS. Organs will be perfused through a recently developed machine perfusion device from the beginning of back-table procedures until implantation, without increasing cold ischemia time (CIT). The aim of the study is to demonstrate the ability of HOPE to improve graft function and post-operative outcomes of ECD kidney and liver recipients.

## Methods

### Study Design

In an open-label, single-center, randomized clinical trial, we will compare HOPE (study group) to SCS (control group) in ECD KT and LT. In the HOPE group, 55 livers and 55 kidneys will be preserved by SCS at 4-10°C from the end of organ retrieval until arrival at the transplant hospital. Afterwards, grafts are preserved with HOPE at 4-10°C for a minimum of 1 hour for livers and 2 hours for kidneys until implantation in the recipient. HOPE starts during back-table graft preparation. During the back-table procedure, organs are flushed with a preservation fluid (Belzer solution). Then, the organ is perfused with HOPE through a closed recirculating system.

In the SCS group, 55 livers and 55 kidneys will be preserved by SCS at 4-10°C from the end of the organ retrieval until implantation in the recipient.

In this study, 220 patients will be enrolled, with 55 in each of the following groups: LT-HOPE, LT-SCS, KT-HOPE, and KT-SCS.

The trial design is outlined in Table 1, and the protocol algorithm is shown in Figure 1.

Based on the number of transplants usually performed at the participating center, this clinical study is estimated to be accomplished in 2 years, including 12 months of patient enrollment and 12 months of follow-up. Enrollment at the Bologna Transplant Center started in January 2019 and will end in January 2020 (Figure 2).

**Table 1 table1:** Trial design to evaluate the benefit of end-ischemic hypothermic oxygenated perfusion (HOPE) on extended criteria donor grafts for livers and kidneys as compared with static cold storage (SCS), N=220.

			Study group (HOPE)		Control group (SCS)
Number of livers			55		55
Number of kidneys			55		55
**Process flow**					
	Step 1.		Preservation in SCS at 4-10°C		Preservation in SCS at 4-10°C
	Step 2.		Transfer to the transplant hospital		Implantation in the recipient
	Step 3.		Preservation with flushing and HOPE for 30-40 minutes		N/A
	Step 4.		Preservation with HOPE at 4-10°C for 1-3 hours		N/A
	Step 5.		Implantation in the recipient		N/A

**Figure 1 figure1:**
[figure not shown]
The protocol algorithm for treatment of the study group undergoing preservation with hypothermic oxygenated perfusion (HOPE).

**Figure 2 figure2:**
[figure not shown]
Estimated 2-year timeline to conduct the study, with enrollment at Bologna Transplant center starting in January 2019 and ending in January 2020.

### Study Population

#### Donor and Patient Selection

Donors are considered eligible for the trial if they meet the United Network for Organ Sharing criteria for ECD. For kidneys, these include donor age ≥60 years or 50-59 years plus 2 or more of the subsequent risk factors: death due to cerebrovascular accident, history of hypertension, donor serum creatinine >1.5 mg/dL, or CIT >20 hours. For livers, these include hemodynamic deterioration, donor age >65 years, donor BMI >30 kg/m^2^, serum bilirubin >3 mg/dL, aspartate aminotransferase (AST) or alanine aminotransferase (ALT) >3 times the upper reference threshold, sodium >165 mmol/L, intensive care unit stay >7 days, steatosis >40%, or CIT >12 hours [12,13].

Exclusion criteria include donor age ≤18 years, split-liver recipients, LT for acute liver failure, pre-emptive renal transplant, and intraoperative surgical complications before the organ implantation. Donors after circulatory death will also be excluded, because Italian law requires 20 minutes of a “no touch period” before the death declaration, causing prolonged warm ischemia and subsequent mandatory perfusion of the organ [14].

All adult (age ≥18 years) patients waitlisted for LT or KT will be enrolled in the study after providing written informed consent.

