#### Randomization

Patients are randomized 1:1 to the HOPE and SCS groups according to the treatment list produced by the randomizer tool. For KT, patients are stratified according to the duration of CIT before HOPE starts (longer or shorter than 12 hours); grafts with CIT >20 hours are excluded from the study. For LT, patients are stratified according to the contemporary presence of ECD liver criteria (more or less than 5 criteria). The study information and informed consent form are distributed to potential recipients. Randomization is performed for patients who sign the consent form after the organ is deemed suitable for transplantation.

To favor comparison between paired kidneys, when both kidneys from the same donor are allocated to the same center, grafts are automatically assigned to a study group and the corresponding control group. Furthermore, in cases where there are multiple transplants occurring at the same time, we prioritize LT over KT, to reduce the CIT.

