#### Hypothermic Oxygenated Machine Perfusion

Organ perfusion is conducted with the Vitasmart (Medica, Bologna, Italy) machine, expressly designed for ex vivo perfusion of abdominal organs [7]. This machine system consists of two pumps, one heat exchanger, and three flow and pressure probes (Figure 2). The sterile disposable perfusion set is composed of a membrane oxygenator, tubing for vessel cannulation, and surgical cannulas.

Kidney perfusion is performed through the renal artery at a pressure of 25-30 mm Hg. Liver perfusion is performed through the portal vein at a pressure of 5 mm Hg.

Flow, pressure, and temperature are monitored and stored on a USB memory device during organ perfusion. Gas analysis of the effluent perfusate is accomplished at the start of perfusion (T0) and then every 30 minutes to determine carbon dioxide partial pressure, oxygen partial pressure (pO_2_), pH, and lactate levels. Two perfusate samples are collected at the beginning and at the end of perfusion to rule out bacterial or fungal contamination.

Graft perfusion is performed in the operating room, from the start of the back-table preparation to organ implantation. First, each organ is connected to the perfusion device through cannulation of the vessels with appropriately sized cannulas. HOPE starts by flushing the organ at low flow values (20 mL/min) with new oxygenated perfusion fluid during the back-table preparation, with the aim of removing waste products and residual microthrombi. After the back-table preparation is completed, the organ is treated with continuous HOPE until transplant. Organ perfusion is continuously monitored. As previously reported [7,8], minimal perfusion time is 1 hour for livers and 2 hours for kidneys.

Belzer machine perfusion solution (2 L, kidneys; 3 L, livers) at 4-10°C, in sterile conditions, and with continuous oxygenation (pO_2_ of 500-600 mm Hg) is used for perfusion.

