### Ethical Review

The research protocol, including the forms for data treatment, study information, and participant content forms, were approved by the Emilia-Romagna Region Ethics Committee, which is the ethics committee for the transplant center, and the National Health System Research.

Written, informed consent is obtained prior to final enrollment. Randomization is performed as recommended by the ethics committee, and all members of the research team learns the treatment type of each recipient only after their inclusion. Possible protocol changes will be applied after the approval of their amendments by the National Health System Research and then the local ethics committee.

Recipients are insured against study-related adverse events with a protocol-specific insurance policy.

The principal investigator and all members of our research scientific group have declared no conflict of interest.

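### The exclusion for intraoperative complications before implantation can be applied after randomization, with the arm known, so it permits unblinded post-randomization exclusions

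*Protocol article*

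**What the plan says.** - **Protocol article, Donor and Patient Selection.** The exclusion criteria include "intraoperative surgical complications before the organ implantation". The phrase comes directly after three recipient criteria (split-liver recipients, transplantation for acute liver failure, pre-emptive renal transplant). The article does not define which complications qualify or who decides.
- **Randomization.** "Randomization is performed for patients who sign the consent form after the organ is deemed suitable for transplantation". Allocation is 1:1. When both kidneys of a donor come to the center, "grafts are automatically assigned to a study group and the corresponding control group".
- **Hypothermic Oxygenated Machine Perfusion.** "Graft perfusion is performed in the operating room, from the start of the back-table preparation to organ implantation". The same section states that "minimal perfusion time is 1 hour for livers and 2 hours for kidneys".
- **Study Design.** "In an open-label, single-center, randomized clinical trial, we will compare HOPE (study group) to SCS (control group) in ECD KT and LT".
- **Ethical Review.** "all members of the research team learns the treatment type of each recipient only after their inclusion".

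**The concern.** An exclusion criterion protects the comparison only if it is settled before the arm is assigned. This one covers events up to implantation. If such an event follows randomization, removing the patient means that the groups compared are no longer the groups randomized. The decision is also made by people who know the arm, without a definition to hold them to.

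Recipients with a surgical complication are plausibly at higher risk of EAD, DGF, PNF and a long stay. Their removal may therefore be related to the outcome. If it also differs by arm, both primary comparisons are biased. For kidneys there is a further cost: excluding one recipient of a donor pair breaks the paired comparison that the Randomization section sets out to favor.

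**Working it through.** **Order of events.** No sentence gives the whole sequence, so it has to be assembled:

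1. The organ is accepted, and the consenting recipient is randomized (Randomization).
2. The team learns the arm after inclusion (Ethical Review), and nothing conceals it from then on (Study Design: open label).
3. In the HOPE arm, perfusion starts with the back-table preparation (Study Design; Hypothermic Oxygenated Machine Perfusion). The arm must be assigned by then.
4. HOPE runs for at least 1 hour (liver) or 2 hours (kidney) and ends at implantation.
5. The exclusion criterion can be met at any time up to implantation.

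Steps 3 to 5 put at least the last 1 to 2 hours of the criterion's window after allocation in the HOPE arm. SCS patients are randomized at the same decision point, so their window also runs past allocation, though the article gives no minimum length for it.

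**Size.** The article has no figure on this point to reproduce: it gives neither a complication rate nor a number of exclusions. What follows shows sensitivity and is not an estimate.

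Inputs, from Study Design and Sample Size Calculation: 55 livers per arm, with EAD expected at 20% (SCS) and 10% (HOPE). Expected events are 55 × 0.20 = 11 and 55 × 0.10 = 5.5; 6 is used for HOPE.

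The uncorrected chi-square is (p1 − p2)² / [p(1 − p)(1/n1 + 1/n2)], where p is the pooled proportion.

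- *All patients kept*, 11/55 vs 6/55: p = 17/110 = 0.1545; 0.0909² / [0.1545 × 0.8455 × (1/55 + 1/55)] = 1.74, P=.187.
- *Three HOPE patients with EAD removed*, 11/55 vs 3/52: p = 14/107 = 0.1308; 0.1423² / [0.1308 × 0.8692 × (1/55 + 1/52)] = 4.76, P=.029. Fisher's exact test gives .043 and the continuity-corrected chi-square .058.

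Other assumed patterns of removal, all with the uncorrected test:

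| Patients with EAD removed | SCS vs HOPE | P |
|---|---|---|
| None | 11/55 vs 6/55 | .19 |
| Two from HOPE | 11/55 vs 4/53 | .06 |
| Three from HOPE | 11/55 vs 3/52 | .03 |
| Three from each arm | 8/52 vs 3/52 | .11 |
| Three from SCS | 8/52 vs 6/55 | .49 |

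**Type I error.** With no true effect and 55 per arm, 400,000 simulated trials were run (uncorrected chi-square, two-sided 5%). In each, k HOPE patients who would have had the event were removed, and no SCS patients.

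| k | EAD, 20% in both arms | DGF, 50% in both arms |
|---|---|---|
| 0 | 5.1% | 4.5% |
| 3 | 11.9% | 6.6% |
| 5 | 24.2% | 9.0% |

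The liver comparison is the more sensitive because it rests on fewer events.

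**The case against.** **The order is inferred, and the phrase may refer to the donor operation.** The article does not say whose operation is meant, and the list also contains a donor item (age). Complications at retrieval would precede randomization. This reading is possible but strained: the phrase follows recipient criteria, and its end point is implantation, which is an event in the recipient.

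**Eligibility is closed earlier.** The Organ Retrieval section keeps organs on ice until the final decision on donor and recipient eligibility. But a criterion that runs up to implantation cannot be fully settled at that point.

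**The analysis set belongs elsewhere.** The article does not say that randomized patients who meet the criterion are dropped from the analysis, and an SAP could address this. However, the criterion itself is fixed here, and an analysis set that kept these patients would contradict it as worded.

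Three stronger readings are tempting, and the documents do not support them:

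- *That one arm loses its bad-risk patients.* The criterion applies to both arms, and nothing states or shows a one-sided loss.
- *That HOPE recipients are exposed for longer.* HOPE has a minimum perfusion time and SCS has none, but the Abstract, Introduction and Discussion say that cold ischemia time is not increased. A minimum perfusion time does not show a longer operation before implantation.
- *That three exclusions are enough to turn the result.* This takes half of the HOPE arm's six EAD events and none from SCS, and it depends on the test: with continuity correction P is .058. The Statistical Tests section says only that chi-squared tests are used. Removing patients from SCS instead moves the result the other way.

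**Conclusion.** The point holds as a fault in the rule: as worded, the criterion allows patients to be excluded after randomization by people who know the arm. This rests on the recipient reading of the phrase and on the order of events above, which is firm for the HOPE arm.

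Bias in the EAD or DGF comparison is possible but not established. It arises if exclusions differ by arm or relate to outcome. If they are balanced and unrelated to outcome, the loss is mainly power. The direction is not determined, and the size is unknown without a complication rate. The worst-case figures show only that, with about 11 and 6 expected EAD events, a handful of one-sided exclusions could matter. DGF is less sensitive.

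**What to change.** 1. Delete the phrase from the exclusion criteria, or limit it to events judged before randomization.
2. Analyse all randomized patients in the assigned arm, regardless of such complications and of the preservation actually received. Limiting the primary analysis to patients who received the allocated graft would again condition on an event after randomization.
3. Report by arm, with reasons, any randomized patient who is not transplanted and so has no graft outcome.
4. Present the analysis without patients who had these complications only as a sensitivity analysis.

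The cost is a short amendment with the approvals named under Ethical Review (National Health System Research, then the local ethics committee), restoring the data of any patient already excluded, and slightly noisier outcomes. The article reports 108 participants already recruited, so it should be checked before analysis whether anyone has been excluded under this criterion.

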#### Randomization

Patients are randomized 1:1 to the HOPE and SCS groups according to the treatment list produced by the randomizer tool. For KT, patients are stratified according to the duration of CIT before HOPE starts (longer or shorter than 12 hours); grafts with CIT >20 hours are excluded from the study. For LT, patients are stratified according to the contemporary presence of ECD liver criteria (more or less than 5 criteria). The study information and informed consent form are distributed to potential recipients. Randomization is performed for patients who sign the consent form after the organ is deemed suitable for transplantation.

To favor comparison between paired kidneys, when both kidneys from the same donor are allocated to the same center, grafts are automatically assigned to a study group and the corresponding control group. Furthermore, in cases where there are multiple transplants occurring at the same time, we prioritize LT over KT, to reduce the CIT.

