#### Statistical Tests

The continuous variables will be compared using parametric (ANOVA) or non-parametric (Kruskal-Wallis) tests according to the data distribution, and the categorical variables will be compared using chi-squared tests. Multivariate analysis will be performed using forward stepwise logistic regression analysis. Survival analysis will be conducted using the Kaplan-Meier method. *P* values <.05 will be considered statistically significant.

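### Same-donor kidneys are split between arms to allow a paired comparison, but only independent-sample tests are named, so the kidney analysis is conservative and loses power

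*Protocol article*

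**What the plan says.** All of this is in the protocol article.

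- **Randomization, general rule.** "Patients are randomized 1:1 to the HOPE and SCS groups according to the treatment list produced by the randomizer tool". Kidney recipients are stratified by cold ischemia time (CIT): "For KT, patients are stratified according to the duration of CIT before HOPE starts (longer or shorter than 12 hours"). On timing: "Randomization is performed for patients who sign the consent form after the organ is deemed suitable for transplantation".
- **Randomization, pair rule.** The aim is given as "To favor comparison between paired kidneys". The rule itself reads "when both kidneys from the same donor are allocated to the same center, grafts are automatically assigned to a study group"; the mate goes to the control arm.
- **Statistical Tests.** For binary outcomes, "the categorical variables will be compared using chi-squared tests". Continuous outcomes go to ANOVA or Kruskal-Wallis, multivariable work to forward stepwise logistic regression, and survival to Kaplan-Meier. No paired, conditional or donor-clustered method is named.
- **Sample Size Calculation.** The kidney assumption is DGF of 50% on static cold storage (SCS) against 30% on HOPE, two-sided alpha .05, power 80%. Study Design gives 55 kidneys per arm. Pairing is not mentioned in the calculation.

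**The concern.** Design and analysis disagree. Putting the two kidneys of one donor in opposite arms removes donor-to-donor variation from their contrast. That benefit reaches the p-value and confidence interval only if the analysis knows which kidneys belong together. The chi-squared test uses a variance that assumes no link between the arms. If pair mates' outcomes are positively correlated, which is plausible because they share the donor, the true variance of the difference is smaller than the test supposes.

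What is at stake is precision. The kidney comparison is already short of its stated power, and the design contains information that the named tests leave unused. This is more than detail left to an analysis plan, because the article itself names the tests, and they do not deliver the comparison that the pair rule was introduced to favor.

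**Working it through.** **Inputs from the article.** DGF 50% (SCS) and 30% (HOPE); two-sided alpha .05; 80% power; n = 55 kidneys per arm.

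**Inputs assumed, because the article does not give them.** Within-donor correlation of DGF, ρ, from 0 to 0.4. Share s of kidneys in split pairs, 50% or 100%.

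**Step 1: the plan's own figure.** The usual two-proportion formula gives

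n = [1.96·√(2·0.4·0.6) + 0.842·√(0.25 + 0.21)]² / 0.2² = (1.358 + 0.571)² / 0.04 ≈ 93 per arm,

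or 98 to 104 after allowing for 5-10% dropout. The planned 55 is not reproduced. At 55 per arm:

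- null standard error: √(2·0.4·0.6/55) = 0.0934
- standard error under the alternative: √(0.46/55) = 0.0915
- power: Φ[(0.2 − 1.96·0.0934)/0.0915] = Φ(0.185) ≈ 57%

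Simulation of the chi-squared test gives about 58%. The shortfall against 80% is a separate sample-size matter; here it is only the baseline.

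**Step 2: effect of splitting pairs.** With share s of the kidneys in split pairs,

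Var(difference) = [0.25 + 0.21 − 2sρ·√(0.25·0.21)]/55.

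Since 2·√(0.25·0.21) = 0.458, almost equal to 0.46, the variance is about f·0.46/55 with **f = 1 − sρ**.

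**Step 3: consequences.**

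- True size of the chi-squared test: 2·[1 − Φ(1.96/√f)].
- Power of an analysis that uses the correct variance: Φ[(0.2/√f − 1.96·0.0934)/0.0915].

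| Share paired | ρ | f | Chi-squared true size | Donor-aware power |
|---|---|---|---|---|
| any | 0 | 1.00 | 5.0% | 57% |
| 50% | 0.1 | 0.95 | 4.4% | 60% |
| 50% | 0.3 | 0.85 | 3.3% | 64% |
| 50% | 0.4 | 0.80 | 2.8% | 67% |
| 100% | 0.1 | 0.90 | 3.9% | 62% |
| 100% | 0.3 | 0.70 | 1.9% | 73% |
| 100% | 0.4 | 0.60 | 1.1% | 79% |

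**Step 4: check by simulation.**

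- Chi-squared size with half paired: 4.4%, 3.3% and 2.8-2.9% at ρ of 0.1, 0.3 and about 0.4. With all paired: 3.9%, 2.0% and 1.2% at 0.1, 0.3 and 0.4.
- Chi-squared power stays at 58-59% throughout this range.
- Donor-clustered standard errors with half paired: power 62%, 65% and 67% at ρ of about 0.18, 0.29 and 0.38.
- McNemar's test with all paired: power 63%, 73% and 79-80% at ρ of 0.1, 0.3 and 0.4.

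The formulas and simulations agree to within about one point.

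**The case against.** **The error is on the safe side.** True: the chi-squared size stays at or below 5%, so no false-positive risk arises. Splitting pairs also balances donor factors across arms whatever test is used. The pairing is therefore not useless; its benefit is left out of the inference.

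**The size rests on two unknowns.** Also true. With half paired and ρ = 0.1, or a quarter paired and ρ = 0.2, f is 0.95 and the gain is about two points. Pairing is conditional on both kidneys coming to the center, so the 100% case is an upper bound. Within the range examined, donor-aware analysis does not by itself restore 80%.

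**Stronger readings the article does not support.**

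- A reader might infer that pairs are assigned automatically instead of at random, outside the list. The wording fits equally well with one random draw per pair and the mate taking the opposite arm, which is a valid randomized paired design. The article leaves the draw unstated; it does not say that anyone chooses.
- A reader might infer a contradiction with the Ethical Review section, where "all members of the research team learns the treatment type of each recipient only after their inclusion", because one mate's arm reveals the other's. If both recipients are fixed and consented before the draw, this does no harm. Randomization is placed after consent and organ acceptance, and nothing says otherwise for pairs.
- A reader might infer that arm is confounded with implantation order. That requires staff to choose which kidney is perfused, and no section says they do.

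**Conclusion.** The point holds as a mismatch between design and analysis. Same-donor kidneys are split on purpose, and the named tests ignore the link. With positive within-donor correlation the kidney DGF test is conservative and gives up power.

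Assuming half the kidneys are paired and a correlation of 0.1 to 0.4, the true size is about 4.4% to 2.9%, and a donor-aware analysis would move power from about 58% to about 60-67%. If all are paired it would reach about 63-79%. At zero correlation there is no gain. The direction is certain for any positive correlation; the amount is not, because neither the correlation nor the paired share is documented.

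The change is worth making because it is cheap and uses information that the design already creates. It is not a threat to validity. The unstated random step within pairs is a matter for clarification and is not evidence of non-random allocation.

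**What to change.** 1. **Analysis.** For kidney DGF, replace the plain chi-squared test with a method that uses pairs and single kidneys together: for example GEE or a mixed logistic model with donor as cluster, and treatment and CIT stratum as fixed terms. Report the risk difference with donor-clustered standard errors. McNemar's test or conditional logistic regression can support the pairs, but should not be the main analysis because they drop the single kidneys.
2. **Data.** Record a donor-pair link. Data Management describes a code per transplant but no link between mates, so pairs already transplanted would need it added retrospectively.
3. **Clarification (secondary).** State that one concealed random draw per pair decides which kidney gets HOPE, after both recipients are fixed and consented. State also how this fits the treatment list and the CIT strata, since mates could fall on different sides of 12 hours.

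**Cost.** No extra patients, and slightly more model complexity. The article reports 108 of 220 recruited in an open-label trial, which is past the 60-patient interim trigger. The change should therefore be made by dated amendment, justified by the design and not by accumulating results. A new wording of the pair rule cannot alter pairs already assigned.
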